#### Feasibility outcomes

Recruitment and retention – 1) What proportion of approached schools decided to take part in the trial? 2) What proportion of recruited schools remained in the trial? 3) What proportion of eligible pupils are opted out of the trial by parents/guardians? 4) Are schools willing to be randomly assigned (Yes/No)? These questions will be answered using our ongoing school recruitment and retention tracking data.

Fidelity – 1) Are teachers able to implement and adhere to the KiVa-SEND programme with a good level of fidelity (data on percentage adherence to lesson plans)? 2) Are the manualised lesson plans and activities acceptable to the teaching staff (Yes/No – with suggested changes)? These questions will be answered using the post-lesson teacher reporting data.

Staff surveys – Are staff willing and able to complete the outcomes measures (perceived bullying of each pupil; mental health of each pupil) (Yes/No)? This question will be answered based on the number of returned questionnaires.

Pupils – Are pupils able to understand and complete the outcome measures (experience of bullying involvement) (Yes/No)? This question will be answered based on the number of returned questionnaires and on feedback from researchers supporting the completion of pupil questionnaires.

Adherence/attendance – What was the range of pupil attendance to all of the KiVa-SEND lessons. This question will be answered using our post-lesson teacher reporting data on pupil attendance.

Anti-bullying programmes – How is the usual practice of anti-bullying programmes and procedures different from KiVa-SEND? This question will be answered using school anti-bullying policies and data gathered from the school.

### Process evaluation

The project will follow MRC guidelines on process evaluations for complex interventions [13] to explore a) recruitment and retention, b) implementation and adherence of the adapted KiVa programme, c) engagement and acceptability of/to pupils and staff, and d) suitability of the outcome measures. This will help us to shape the research design and methods for a definitive trial. Interviews will be audio-recorded, transcribed, and thematically analysed.

Teaching staff – Three to six semi-structured interviews will be conducted with teaching staff: one to two from one to two comparison schools and two to four from two to four intervention schools. Interviews will build on the tracking data and post-lesson teacher survey data to explore in more depth the school experience of sign-up to the study, their thoughts on supporting school retention, acceptability of the research design and adherence to materials.

Pupils – Up to 10 semi-structured interviews or Talking Mats sessions will be conducted with pupils from interventions schools. Sessions will explore enjoyment and engagement of the lessons, materials, activities and questionnaires.

Framework analysis will be applied to the interview and focus group data, informed by the feasibility questions and the MRC process evaluation framework.

### Data management, security, and confidentiality

Data entry, coding, security, storage and confidentiality will be ensured, in line with GDPR. Only the trial team will have access to the final study dataset.

All pupil and staff names and school names will be stored securely in password protected documents on the researchers’ secure University of Oxford Nexus 365 SharePoint, separate from any trial data. Pupil questionnaire responses will be collected electronically on trial tablets, via the offline Qualtrics application. Once back at the University, the tablets will be connected securely to the Internet and the offline Qualtrics application will be become online, and the data file will be exported to the researchers’ secure University of Oxford Nexus 365 SharePoint. All data will be pseudonymised, inputted with pupil codes instead of names. Paper versions will be available as back-ups in case of technical issues or pupil preference or need. Teacher questionnaire responses will be collected on paper. All paper data copies will be transferred to the University and stored securely in locked cupboards before being entered into the electronic database. Once data has been entered and checked, the original paper copies will be securely shredded.

Interview and Talking Mats audio recordings will be recorded on audio-recorders. The files will be transferred to the researchers’ secure University of Oxford Nexus 365 SharePoint before being transcribed. Once transcribed, anonymised and checked, the original audio files will be deleted. Framework analysis will be used for the analysis of these qualitative data sets.

All data will be password protected and kept secure. The linkage list (linking pupil name with pupil ID) is required to match summer 2025 and summer 2026 data. This list will be password protected and kept separately to all other collected data (which will be anonymous).

No formal data monitoring committee (DMC) is required due to the nature of this feasibility trial. Instead, the trial team will ensure data monitoring and quality assurance.

### Progression criteria

The assessment of whether this feasibility study can later progress to a full definitive study will be determined by several criteria. Progression thresholds of these criteria are set out in Table 2 and following these categorisations: 1) Green: proceed to a full study without modification, 2) Amber: proceed to a full study with caution and some modification, 3) Red: unsuitable to proceed to a full study.

**Table 2 Tab2:** Progression thresholds to determine suitability of the KiVa-SEND study to progress to a later full definitive study

	Green	Amber	Red
Recruitment of approached schools	≥ 60%	40–59%	≤ 39%
Eligible pupils recruited *	≥ 80%	60–79%	≤ 59%
Baseline pupil data collected	≥ 80%	60–79%	≤ 59%
Baseline teacher data collected	≥ 90%	70–89%	≤ 69%
Number of classes reaching adherence to the KiVa-SEND programme†	≥ 90%	70–89%	≤ 69%
Number of classes reaching delivery fidelity of KiVa-SEND components‡	≥ 80%	60–79%	≤ 59%
Retention of schools at 12-month follow-up	≥ 90%	70–89%	≤ 69%
Follow-up pupil data collected of those still attending the school	≥ 80%	60–79%	≤ 59%
Follow-up teacher data collected for pupils still attending the school	≥ 90%	70–89%	≤ 69%

^*^Eligible pupils are those within the specific classes pre-selected by the school to participate in the KiVa-SEND study. Recruitment of these pupils is determined by whether their parent / guardian opted them out of participating

^†^Adherence is based on at least 70% of lessons (14/20) being delivered to each participating class (max = 20 lessons over one academic year)

^‡^Fidelity is based on at least 80% of lesson components being delivered per lesson to each participating class (components vary between three and six per lesson)

Other data will be used to inform whether progression to a full definitive randomised controlled trial is feasible, including.Recruitment and retention, as identified in Table 2, but also process evaluation data will be examined for specific details such as barriers and facilitating factors.Adherence and delivery (implementation) as identified in Table 2, but also post-lesson teacher reporting data and process evaluation data will be examined for specific details such as barriers and facilitating factors at the teacher and at the pupil level.Engagement and acceptability of the programme, post-lesson teacher reporting data and process evaluation data will be examined for specific details such as barriers and facilitating factors at the teacher and at the pupil level.Suitability of potential outcome measures for pupils and staff based on process evaluation data and researcher field notes of pupil comprehension, examined for specific details such as barriers and facilitating factors.

In all cases, recommendations will be incorporated into a future full study protocol.

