## Methods

### Aims

The primary aim is to examine the feasibility of the KiVa-SEND anti-bullying programme being delivered successfully by teachers to pupils in special education schools, with a focus on recruitment and retention, implementation and adherence, engagement and acceptability.

The secondary aim is to examine the suitability of potential outcome measures for pupils and staff.

Combined, these will determine the feasibility to later conduct a definitive randomised controlled trial of the effectiveness of KiVa-SEND.

As a feasibility study, no hypotheses are generated. However, the following feasibility outcome data will be collected: Primary outcomes – 1) recruitment and retention, 2) adherence to the programme, 3) staff survey completion, 4) pupil survey completion. Secondary outcomes – 1) pupil self-report data on bullying involvement, 2) staff data on pupil mental health and pupil involvement in bullying, 3) differences in teaching content and action processes to tackle bullying, between all schools’ usual anti-bullying practice, and the KiVa-SEND practice.

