### Sample size

Data will be collected from 2 – 6 classes per school. With an average of 8 pupils per class, the pupil sample size is 296. With eight schools and a range of 2- 6 classes per school, the teacher sample size is estimated to be between 16 and 96 depending on whether the same teacher is present for the baseline and follow-up data collection. In total, between three and six teachers will participate in the process evaluation interviews, and up to 10 pupils will participate in the process evaluation interviews or Talking Mats. As a feasibility trial to inform a definitive trial we proposed recruiting sufficient schools and pupils to address our feasibility questions, and particularly the question regarding retention of pupils. With a baseline sample size of 296 children and a potential retention rate of 75% (middle of our amber progression thresholds) a 95% CI of 0.05 would be 70%—80% [7]. Recruiting eight schools as stipulated (four in each trial arm), will ensure that even if we experience whole-school drop-out, expected pupil attrition or refusal, or missing pupil or teacher data, we will still be able to conduct our trial with enough data to provide informative findings.

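### The trial is sized on retention of all 296 baseline pupils, but no feasibility question or progression row measures that proportion, so pupils who leave their school do not count in the progression rule

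*Protocol article*

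**What the plan says.** The Sample size section gives the purpose of the sample as answering the feasibility questions, "particularly the question regarding retention of pupils". Its calculation runs: "With a baseline sample size of 296 children and a potential retention rate of 75" per cent, with the 75% described as the "middle of our amber progression thresholds", and then "a 95% CI of 0.05 would be" 70% to 80%. The quantity is therefore retention out of all baseline pupils, and the text implies that it has a progression threshold.

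The Aims section lists "Primary outcomes – 1) recruitment and retention, 2) adherence to the programme" and further items, without giving a unit or denominator for retention. The Feasibility outcomes section turns recruitment and retention into four questions: school uptake, "What proportion of recruited schools remained in the trial", "What proportion of eligible pupils are opted out of the trial by parents/guardians", and willingness to be randomised. The one retention question is about schools. The one pupil-level question is about opt-out at entry.

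Table 2 (Progression criteria) has three follow-up rows. One is retention of schools. The second is "Follow-up pupil data collected of those still attending the school" (green from 80%, amber 60–79%, red to 59%). The third is teacher data, also limited to pupils who have not left (green from 90%, amber 70–89%, red to 69%). The text after Table 2 refers back to it for retention and adds detail on barriers and facilitators from the process evaluation.

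**The concern.** The quantity that justified the sample size has no place in the decision rule. A pupil who changes school during the year leaves both the numerator and the denominator of the pupil-level follow-up rows, so the rows cannot respond to pupil mobility, whatever its extent.

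This matters because the cohort is closed. The eligibility criteria exclude pupils who join after baseline, so leavers are not replaced, and follow-up falls in the next school year. The planned exploratory comparison uses follow-up data with baseline as covariate and no imputation, so a pupil without follow-up data is lost to it. A definitive trial of the same form would depend on the share of baseline pupils with both measurements. As written, the pupil row can signal that a full study may go ahead unmodified while that share is amber or red on the same cut-offs.

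**Working it through.** **Inputs.** n = 296 and retention p = 0.75 with half-width 0.05 (Sample size); pupil bands 80/60 and teacher bands 90/70 (Table 2). The leaver share L is not given anywhere, so the values below are assumptions.

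**1. The plan's own figure.** Half-width = 1.96 × √(0.75 × 0.25 / 296) = 0.0493, giving 70.1% to 79.9%. In reverse, n = 1.96² × 0.1875 / 0.05² = 288.1, or 289 rounded up, against 296 stated. The stated interval reproduces, with all 296 baseline pupils as denominator. (It treats pupils as independent across schools; that is a separate matter and is not used here.)

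**2. Which amber band has 75% as its middle?**
- 40–59%: 49.5%
- 60–79%: 69.5%
- 70–89%: 79.5%

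None does. Only the pooled span 60–89% comes close, at 74.5%. The 75% cannot be traced to any one row.

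**3. What the pupil row shows.** Let C be completion among pupils who stay. The row reports C. Retention of the baseline sample is R = (1 − L) × C.

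**4. The planning case.** With R = 0.75, the row is green when 0.75 / (1 − L) ≥ 0.80, that is L ≥ 1 − 0.75/0.80 = 0.0625. Since 0.0625 × 296 = 18.5, 19 leavers are needed (19/296 = 6.4%). Check: 222/(296 − 19) = 222/277 = 80.1%, green. With 18 leavers, 222/278 = 79.9%, just short.

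**5. Completion just at the green limit.**

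| Assumed leavers | Stayers | With follow-up data | Table 2 row | Out of 296 |
|---|---|---|---|---|
| 10% | 266 | 213 | 80.1% green | 72.0% |
| 20% | 237 | 190 | 80.2% green | 64.2% |
| 26% | 219 | 176 | 80.4% green | 59.5% |
| 30% | 207 | 166 | 80.2% green | 56.1% |

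On the 80/60 bands the first two all-baseline figures are amber and the last is red. In general (1 − L) × 0.80 < 0.60 when L > 0.25.

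**6. Completion at its best.** If every stayer is measured, 20% leavers gives 237/296 = 80.1%, still green on an all-baseline denominator; 30% gives 207/296 = 69.9% and 50% gives 148/296 = 50.0%. The row would read 100% in all three cases.

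**The case against.** The restricted denominator is stated openly in the row label and has a sound purpose: it asks whether data can be collected from pupils who can be reached, and so separates failure of trial procedures from pupils changing school. That stands, and it is a reason to keep the row. Whole-school withdrawal is also counted, by the school-retention row, so only individual leavers go unseen.

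A reader might infer that pupil attrition will go unreported. The article does not support that. Missing data are to be reported, and a linkage list is kept to match the two time points, so the all-baseline proportion can be derived. Nor does it follow that the definitive sample size must be wrong: it could use the observed attrition rather than the colour of a row, and the article says that other data will also inform progression.

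A reader might also infer that attrition will be heavy. No leaver rate is given, and red at 80% completion needs more than 25% leavers. Multiplying the green limits of successive pupil rows to project a low yield of paired data is not supported either, because the denominator of the baseline-data row is not stated.

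It may be said that an article condenses a fuller protocol. But the Discussion presents the article as setting out the progression criteria, and the mismatch lies between two things that it states: a sizing quantity tied to an amber threshold, and a table without that quantity. A proportion that can be derived later is not a criterion set in advance.

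**Conclusion.** The point holds. Pupil retention over all baseline pupils sizes the trial and is said to sit in an amber band, yet neither the feasibility questions nor Table 2 contains it, and no single amber band is centred on 75%. Individual leavers are invisible to the progression rule.

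The mismatch is a matter of text and needs no assumption. Its practical size depends on the unknown leaver rate: 6.4% is enough to turn the planning case from amber to green, and more than 25%, with completion at the green limit, takes baseline-sample retention below 60% behind a green row. With few leavers or near-complete follow-up of stayers, the two measures would differ little. No effect estimate or planned analysis is invalidated; what is weakened is the retention part of the progression decision.

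**What to change.** Before follow-up data are examined:

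- Add to Feasibility outcomes and to Table 2: pupils with 12-month pupil data out of all pupils with baseline pupil data. Use the bands already applied to pupil data (green from 80%, amber 60–79%, red to 59%). On these the planned 75% is amber, as the Sample size section says.
- Report leavers by arm. Show losses from withdrawn schools separately, because the school-retention row already counts them.
- Keep the two existing rows restricted to pupils who have not left, as completion measures.
- Report the same all-baseline proportion for teacher data descriptively, without a new threshold.
- State in Sample size which threshold the 75% refers to.
- Report the change as a dated amendment.

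The added row uses data already linked across the two time points. The costs are that a progression criterion is added after baseline and allocation, which must be disclosed, and that the reported retention figure will be less favourable whenever any pupil has left.

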### Benefits and risks

There are minimal risks of the trial and potentially no immediate benefits. It is possible that some pupils may become upset during the data collection on bullying experience, or during the KiVa-SEND lessons, but researchers and teaching staff will always be around to manage and support these situations if they do arise. School safeguarding procedures will be followed, and our research team’s data collection protocol will also be followed in the case of adverse events. It is possible that bullying perpetration and/or bullying victimisation will reduce for those delivering KiVa-SEND (but this study is not aimed to measure that impact). The trial will lead to a better understanding of the feasibility of running KiVa-SEND in special schools, and the potential to begin a definitive randomised controlled trial to test the effectiveness of the programme.

## Discussion

This two-arm feasibility cluster interventional randomised controlled trial with a 1:1 blocked randomisation allocation ratio of eight UK special schools and an embedded process evaluation will evaluate the feasibility of delivering KiVa-SEND – adaptation of the evidence-based Finnish anti-bullying programme KiVa – whilst recognising that generalisability will be limited in relation to pupils with more complex or profound special educational needs. The adherence, fidelity and acceptance of the materials, engagement of teachers and pupils, and the suitability of the outcome measures will be explored. Although this trial will not be testing the effectiveness of the KiVa-SEND programme to reduce bullying and victimisation, it will help to inform whether the questionnaires used to measure these outcomes are suitable for this population. This manuscript details the proposed feasibility study design and the progression criteria required to move to a full definitive study. Any amendments will be included in future publications.

### Publication and dissemination plan

The full feasibility trial results will be published in 2027 once the trial is complete; any protocol modifications will be communicated. Overall and anonymised results will be shared with the schools, who can share with interested parents / guardians. The results will be presented during research talks and conferences.

## Data Availability

This manuscript has no associated data.
